### Nutritional Profile of MB and Placebo Tablets

3.2

For this project, Sen Yuh Farm Science Co. Ltd., Taiwan (https://www.mberrytw.org) donated the MB and placebo tablets. MB tablets consisted of dried MB pulp (55%) and corn starch (45%) as a binding agent. Each tablet weighs 350 mg and contains approximately 0.16 mg of miraculin, according to the donor's report. This content of miraculin is within the range limit of 0.052%–0.32% used previously (Greenaway et al. 2024). The placebo tablets are composed of dragon fruit (20%) and corn starch (80%). Given concerns about the potential toxicity of synthetic food colorants and the corresponding recommendation to favor natural alternatives (Amchova et al. 2024; Malabadi et al. 2022), dragon fruit was incorporated into the placebo formulation to naturally match the color of the MB tablets and thereby support blinding. Table S1 presents the nutritional profile of the MB tablets provided by the donor organization, and the sugar analyses (glucose, fructose, sucrose, maltose, and mannose) of both MB and placebo tablets. Sugar analyses were conducted at the Queensland Alliance for Agriculture and Food Innovation (QAAFI), Centre for Nutrition and Food Sciences (https://qaafi.uq.edu.au/), using an in‐house method with high‐performance liquid chromatography (HPLC). As indicated in Table S1, the analysis indicated that the placebo tablets contained low levels of glucose and fructose, with no detectable sucrose, maltose, or mannose. This finding aligns with existing evidence showing that dragon fruit contains only minimal amounts of glucose and fructose and no detectable sucrose or maltose (Kakade et al. 2022; Tarte et al. 2023), while corn starch contains negligible sugar (Zhang et al. 2021). Therefore, the contribution of the 20% dragon fruit to the overall sugar content of the placebo tablets is considered minimal.

### Eligibility Criteria

3.3

The inclusion and exclusion criteria for all project phases are summarized in Table 2. Rubino et al. (2025) reported that Body Mass Index (BMI) alone is insufficient to define obesity, as it does not differentiate fat mass from lean mass. The recommendations are to confirm obesity through direct measurement of body fat where possible; otherwise, it should be defined as a high BMI combined with at least one additional adiposity indicator (waist circumference [WC], waist‐to‐height ratio [WHtR], or waist‐to‐hip ratio), or the presence of two such indicators irrespective of BMI. In line with this recommendation, we plan to use the WHO age‐, sex‐, and ethnicity‐specific cut‐offs (Barba et al. 2004; Li et al. 2023; Potter et al. 2024; WHO 2008). For this study, a healthy weight is defined as a BMI of 18.5 – 24.9 kg/m^2^ for Europeans and others, or 18.5 – 22.9 kg/m^2^ for Asian populations. Overweight/obesity is defined as a BMI ≥ 25 kg/m^2^ for Europeans and others, or ≥ 23 kg/m^2^ for Asian populations, together with at least one additional criterion: elevated WC (≥ 94 cm for men, ≥ 80 cm for women, ≥ 90 cm for Asian men), WHtR ≥ 0.5, or body fat percentage ≥ 25% for men or ≥ 35% for women, or meet at least two of the additional adiposity criteria. Detailed sex‐ and ethnicity‐specific cut‐offs to be used in Phases 3 and 4 are provided in Table S2.

**TABLE 2 fsn371640-tbl-0002:** Inclusion and exclusion criteria in each phase of the project.

Criteria	Phases 1 and 2	Phases 3 and 4
Inclusion criteria	Adults living in Australia Age 18–65 years Healthy weight BMI	Adults living in Australia Age 18–65 years BMI in the Overweight/Obesity category plus ○ High WC or high WHtR OR ○ High body fat percentage
Exclusion criteria	Known alterations to the sense of smell and taste, including dysphagia SARS‐CoV‐2 infection within the last 3 months Food allergies or intolerances to berries. Current pregnancy or lactation (Turck et al. 2021) Self‐reported non‐communicable disease (Cancer, diabetes, hypertension, and chronic/acute liver disease or kidney problems)	All exclusions proposed for Phases 1 and 2 will apply, except those related to medical conditions. Participants with self‐reported cancer or chronic or acute liver or kidney problems will be excluded. However, those with other stable medical conditions (e.g., controlled diabetes, controlled hypertension, and other chronic diseases) will be eligible to participate in Phases 3 and 4. For Phase 4, as it is a follow‐up study requiring participants to take at least two MB/placebo tablets daily for 3 months, participants with existing medical conditions will be advised to consult their physician prior to confirming enrolment, in case they have unstable conditions (e.g., uncontrolled diabetes, uncontrolled hypertension, or other critical illnesses)

*Note:* Exclusion criteria are based on potential alterations to taste perception that may bias outcome assessment (Bernhardson et al. 2008; Boltong and Keast 2012; Brennan et al. 2020; Duffy 2020; Feng et al. 2014; Kanjanaumporn et al. 2020; Risso et al. 2020).

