
**FIGURE 2 fsn371640-fig-0002:**
[figure not shown]
Phases 2 and three study design.

#### Phase 3

3.7.4

The study design and data collection procedures followed in this phase are identical to those used in Phase 2 (Figure 2). They vary among study participants (Phase 2 is on healthy‐weight adults, and Phase 3 is on overweight or obese adults). A separate investigation is required because taste sensitivity alters with overweight and obesity (Harnischfeger and Dando 2021; Rohde et al. 2020; Vignini et al. 2019). Therefore, the dose of MB required to induce a change in taste perception and food liking may be different for overweight and obese adults than for healthy‐weight adults.

#### Phase 4

3.7.5

This will be a two‐arm, placebo‐controlled, single‐blind, parallel feasibility trial conducted over a 12‐week follow‐up period, in which participants will be blinded to group allocation. Blinding of participants will be maintained via the use of MB and Placebo tablets of similar size and closely matched colourings. Most importantly, participants will only receive their allocated treatment tablets and will not be privy to viewing the alternative treatment tablet. To minimize the risk of unblinding within households, only one participant per household will be enrolled. As this is a feasibility study, the success of blinding will also be evaluated by asking participants at the end of the trial whether they believed they had received MB or placebo.

The participants will have four visits to the Gold Coast campus, or they will be visited at their home by the principal investigator, based on their preference. That is, a first visit (at baseline), a second visit (at the end of the baseline week), a third visit (at the end of the 6th week), and a fourth visit (at the end of the 12th week). The main outcomes of interest are food preferences, energy intake, and dietary quality. Additionally, it will explore its effect on the overall liking of mixed meals (breakfast, lunch, dinner, and snacks) and on appetite. As it is a feasibility study, the other main outcomes of interest will be exploring the feasibility indicators (recruitment, blinding, allocation, retention, compliance, and adverse effects). Furthermore, as a secondary outcome, the study will investigate the effect of MB on anthropometry and body composition. Table 5 indicates the details of the study variables to be measured, including their frequency and the study visits at which they will be assessed.

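### Section 3.3 and Table 2 give different overweight/obesity rules, and under the text one person can qualify both as healthy weight (Phases 1–2) and as overweight/obese (Phases 3–4)

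*Protocol article*

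**What the plan says.** All the rules stand in section 3.3 (Eligibility Criteria) of the protocol article.

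- **Healthy weight, Phases 1 and 2.** In the text, "a healthy weight is defined as a BMI of 18.5" to 24.9 kg/m² (22.9 for Asian populations). Table 2 lists only "Healthy weight BMI". Neither place sets a limit on waist, waist-to-height ratio or body fat, and none of the listed exclusions concerns adiposity.
- **Overweight/obesity in the text, Phases 3 and 4.** The first route is BMI of at least 25 (23 for Asian populations) "together with at least one additional criterion". The criteria are raised waist, waist-to-height ratio of at least 0.5, and raised body fat percentage. The second route follows in the same sentence: "or meet at least two of the additional adiposity criteria".
- **Overweight/obesity in Table 2, Phases 3 and 4.** "BMI in the Overweight/Obesity category plus" a high waist or waist-to-height ratio, or a high body fat percentage. There is no second route.

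The text presents its definition as following a published recommendation, which it reports as accepting high BMI with one further indicator "or the presence of two such indicators irrespective of BMI".

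Section 3.7.4 says that Phases 2 and 3 share design and procedures: "They vary among study participants (Phase 2 is on healthy"-weight adults, and Phase 3 on overweight or obese adults. It justifies a separate Phase 3 by altered taste sensitivity in overweight and obesity, so that the dose needed may differ.

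**The concern.** Two problems follow from setting these rules side by side.

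First, a screener working from the text and a screener working from Table 2 would enrol different people into Phases 3 and 4. Someone with a healthy BMI and two raised adiposity measures is admitted by one and turned away by the other.

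Second, because healthy weight rests on BMI alone, that same person also qualifies for Phases 1 and 2. Eligibility is the only feature that separates Phase 2 from Phase 3. Table 1 gives the two phases overlapping calendar periods (Phase 2 from 1 November 2024 to 30 September 2025; Phase 3 from 1 December to 30 June 2025), and section 3.5 describes one recruitment effort. A volunteer who fits both definitions could be placed in either phase, and no stated rule decides which. What is at stake is whether the labels healthy-weight and overweight/obese mean what a reader of the results will take them to mean.

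**Working it through.** No sample size, power or error rate in the protocol depends on this point, so there is no stated figure to reproduce. The check is logical, with some arithmetic on the cut-offs.

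**Inputs (all from section 3.3).** BMI cut-off 25, or 23 for Asian populations. Waist (W) at least 94 cm for men, 80 cm for women, 90 cm for Asian men. Waist-to-height ratio (R) at least 0.5. Body fat (F) at least 25% for men, 35% for women.

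**Step 1: write the rules as conditions.** Let k be the number of W, R and F that are met.

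- Healthy weight, text and Table 2: healthy BMI, any k.
- Overweight/obese, text: (high BMI and k ≥ 1) or k ≥ 2.
- Overweight/obese, Table 2: high BMI and k ≥ 1.

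**Step 2: enumerate.** Two BMI classes (healthy, high) times 2 × 2 × 2 = 8 criterion patterns gives 16 combinations.

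| BMI class | k | Patterns | Phases 1–2 | Phases 3–4, text | Phases 3–4, Table 2 |
|---|---|---|---|---|---|
| Healthy | 0 or 1 | 1 + 3 = 4 | yes | no | no |
| Healthy | 2 or 3 | 3 + 1 = 4 | yes | **yes** | **no** |
| High | 0 | 1 | no | no | no |
| High | 1, 2 or 3 | 3 + 3 + 1 = 7 | no | yes | yes |

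Text and table disagree in exactly 4 of 16 combinations, and all four are also healthy weight. This counts patterns, which are not equally common. It is not a share of people.

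**Step 3: check that such people can exist.** The body measurements below are assumed for illustration.

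- Non-Asian man, 175 cm, BMI 24, waist 95 cm: 95/175 = 0.543. W and R are met; BMI lies within 18.5–24.9.
- Woman (non-Asian), 160 cm, 61 kg, waist 82 cm: BMI 61/1.60² = 23.8; 82/160 = 0.512. W and R are met.
- Asian man, 170 cm, 65 kg, waist 91 cm: BMI 65/1.70² = 22.5; 91/170 = 0.535. W and R are met.

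Each is eligible for Phases 1–2 (weight criterion), eligible for Phases 3–4 by the text, and ineligible for Phases 3–4 by Table 2.

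**Step 4: how readily the second route is met.** W and R share the waist measurement. At a ratio of 0.5, a waist of 94 cm corresponds to a height of 94/0.5 = 188 cm, and a waist of 80 cm to 80/0.5 = 160 cm. A man of 188 cm or less who meets W at 94 cm, or a woman of 160 cm or less who meets W, therefore meets R as well.

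**Step 5: test the two possible repairs.** If high BMI is always required, Phases 1–2 take the 8 healthy-BMI patterns, Phases 3–4 take 7 high-BMI patterns, and none is shared. If the second route is kept and Phases 1–2 exclude k ≥ 2, Phases 1–2 take 4 patterns, Phases 3–4 take 4 + 7 = 11, and again none is shared. Under either repair the one remaining pattern (high BMI, k = 0) belongs to neither group.

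**The case against.** **The text may be ambiguous instead of contradictory.** The last clause could be attached to the high-BMI condition, and then text and table agree. This reading is weak. Meeting two criteria already implies meeting one, so the clause would do nothing, and it would depart from the recommendation the text says it follows. Even so, wording that allows both readings needs settling.

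**Table 2 is only a summary, and Table S2 is not shown.** Condensation could explain the missing route. But Table S2 is described as giving cut-offs for Phases 3 and 4, so it would not be expected to add an adiposity limit to Phases 1 and 2, and the overlap arises there.

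**The self-reported disease exclusions in Phases 1 and 2 might separate the groups.** They do so only for people who have those conditions.

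**No planned analysis compares the phases.** This stands. Table 6 gives Phases 2 and 3 separate objectives, each comparing doses and placebo within its own phase, and the sample size rests on no between-phase effect. A participant with a healthy BMI and high adiposity does not by that fact bias a dose comparison within a phase.

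**The two waist-based criteria are correlated.** A reader might take Step 4 as a further error in the plan. It is not one: as section 3.3 reports it, the recommendation itself lists waist and waist-to-height ratio as separate indicators. Step 4 shows only that the second route is not remote.

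**Overlapping participants can be identified.** This also stands. Waist and body composition are measured in all phases (Table 3), so the overlap can be described even after enrolment.

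**Conclusion.** The point holds as an inconsistency in eligibility with a consequence for who is enrolled. The text admits people to Phases 3–4 whom Table 2 does not, and each of them also meets the healthy-weight definition for Phases 1–2. This rests on the natural reading of the second route as free of any BMI condition.

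The size in participants is unknown: the document gives no figure for volunteers with a healthy BMI and two raised criteria. For scale only, each arm in Phases 2 and 3 has 10 people, so one such participant is 1/10 = 10% of an arm. The harm is to the population definitions and to any informal comparison of effective dose between Phases 2 and 3.

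Two stronger conclusions are tempting and are not supported. One is that a difference between phases would shrink by some stated share, such as 10–20%. That needs an assumed proportion of overlapping participants and the assumption that they respond like the other phase's population; the document gives neither, and it plans no such contrast. The other is that Phase 3 loses its purpose. The Introduction gives a further reason for the later phases, namely that adults with overweight or obesity are often advised to cut added sugar and eat more fruit and vegetables.

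**What to change.** State one rule, identically in section 3.3, Table 2 and Table S2, that makes the two populations disjoint. Either of these does so:

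1. Remove the BMI-independent route from the text, so that it matches Table 2.
2. Keep that route, add it to Table 2, and exclude from Phases 1 and 2 anyone who meets two or more adiposity criteria.

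If enrolment has begun, state which rule was applied in each phase and report how many participants in each met both definitions.

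The cost is a one-line change to eligibility. No new measurement is needed, since waist and body composition are taken in all phases and section 3.7.3 already confirms eligibility after them. The downside is that a few borderline volunteers change phase or become ineligible.

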### Sample Size

3.4

Table 1 summarizes the sample size for each phase and is determined based on previous effect estimates (Phase 1), the number of fixed‐effect factors to be considered in the regression model (Phases 2 and 3), and the recommended minimum sample size per treatment arm for feasibility studies (Phase 4, Table 2).

#### Phase 1

3.4.1

The sample size is calculated, considering an effect estimate (Cohen's d) of 0.78 from Wong and Kern (2011) on the sweetness taste perception obtained before and after taking MB using G*power software version 3.2, considering 80% power, α level of error of 0.05, and 20% dropout. Using paired sample *t*‐tests, 54 participants (18 in each group) will be recruited.

#### Phases 2 and 3

3.4.2

Determining sample size for mixed models (LMM/GLMM) is challenging, as statistical power depends on multiple factors, including the number of participants, repeated measures per subject, intra‐class correlation (ICC), outcome distribution, and the specified random‐effects structure (Kumle et al. 2021). Given uncertainties, particularly regarding predictors that will ultimately be retained as fixed effects in the final model, the sample size for this study is determined using an empirically informed approach. Consistent with Green (1991) guidelines for regression analyses, for behavioral research with expected large effect estimates, a minimum of 10 participants per predictor variable will be required for included to ensure model stability. In the planned mixed model, treatment (i.e., dose) will be specified as the primary fixed effect, time (pre‐post assessment) as the within‐subject factor, and participant as a random effect. Covariates such as age, sex, and phenylthiocarbamide (PTC) sensitivity will be considered for inclusion to control for potential confounding but will only be retained in the final model if they contribute meaningfully to model stability and fit. Based on an anticipated inclusion of four fixed factors in the final model, a minimum of 40 participants will be recruited for each study phase.

#### Phase 4

3.4.3

Whitehead et al. (2016) recommend feasibility trial sample sizes of 75, 25, 10, and 10 per arm for standardized effect sizes categorized as extra small (< 0.1), small (0.1–0.29), medium (0.3–0.69), and large (≥ 0.7) in a main trial with 80% power and 5% significance. In a randomized crossover trial, Choi and Park (2023) reported medium‐to‐large effect sizes for MB in improving the overall liking of both breakfast (pumpkin oatmeal with banana and blueberries) and dinner (a Korean‐style Baekban meal with rice, soup, and side dishes) in prediabetic and diabetic adults. Therefore, considering a medium to large effect estimate, a minimum of 20 participants (10 per arm) would be sufficient for this feasibility trial. However, in a previous exploratory three‐arm trial evaluating the efficacy and safety of miraculin in 31 cancer patients, attrition of 32% was observed over a three‐month follow‐up (López‐Plaza et al. 2024). To account for this, up to 30 participants (15 per arm) will be recruited. This will satisfy the median sample size target for feasibility studies (Totton et al. 2023).

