### Project Phases and Study Design

3.1

Each phase of the project will use different quasi‐experimental designs. Table 1 presents a summary of the study design, population, setting, variables, sample size, and study period for each phase.

**TABLE 1 fsn371640-tbl-0001:** Study designs, study populations, study settings, study variables, sample size and estimated study periods for each phase of the project.

	Project phases			
	Phase 1	Phase 2	Phase 3	Phase 4
Study design	Three‐arm pre‐post parallel design	Four‐arm placebo‐controlled single‐blind pre‐post parallel design	Four‐arm placebo‐controlled single‐blind pre‐post parallel design	Two‐arm placebo‐controlled, single‐blind (participants), parallel feasibility trial
Study population	Healthy‐weight adults living in Australia	Healthy‐weight adults living in Australia	Overweight or Obese adults living in Australia	Overweight or Obese adults living in Australia
Study setting	Laboratory‐based	Laboratory‐based	Laboratory‐based	In a natural environment (at home)
Independent variable	Different MB doses (175, 350, and 700 mg)	Different MB doses (175, 350, and 700 mg) and placebo	Different MB doses (175, 350, and 700 mg) and placebo	MB or Placebo consumption in a natural environment
Dependent variable	Sour, bitter, tart, and sweet taste perception ratings of food‐based solutions and individual food items	Ratings for sourness and bitterness taste perceptions, overall liking and intake of hypo‐palatable mixed vegetarian salad Ratings for sweetness taste perceptions and overall liking of SSBs	As mentioned in Phase 2	Primary outcomes Food preferences (Overall meal liking and preferences across time) Energy intake Dietary quality Other outcomes of interest Feasibility of the treatment protocol and study procedures Appetite Anthropometry/Body composition
Sample size	54	40	40	30
Proposed study period	1 July–30 September, 2024	1 November 2024–30 September 2025	1 December–30 June, 2025	1 May–30 December, 2025

*Note:* Sociodemographic characteristics (sex*, age, income, employment status, and education status), phenotypic taste perception, genotypic taste sensitivity, mouth pH, anthropometry, and body composition will be collected as covariates. In Phases 3 and 4, comorbidities (e.g., diabetes, hypertension) and medication use (self‐reported) will also be assessed. In Phase 4, physical activity will be measured as a covariate for secondary outcomes. *Sex is classified based on biological characteristics.

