*Note:* For non‐acidic solutions and food items (bitter and tart), we planned to use the solutions mixed with citric acid, as an acidic pH was essential for the taste modification action of miraculin (Doddawad et al. 2022). Food samples were kept in a refrigerator, then removed and placed on separate plastic trays 10 min before each test.

First, sociodemographic characteristics and anthropometric measurements will be collected. Saliva samples will then be obtained for TAS2R38 genotyping, and oral pH and phenotypic taste sensitivity will be assessed. As illustrated in Figure 1, participants (*N* = 54) will subsequently be allocated into three groups (*n* = 18 per group). Prior to commencing the pre‐test session, participants will be instructed to drink a sip of water and wait at least 30 s (Choi and Garza 2020). In their respective groups, participants will receive 10 mL of each solution and pieces of single food items to rate their perceived taste perception on a generalized labeled magnitude scale (gLMS). Participants will rinse their mouths with water between each solution or food item until the previous taste stimulus is gone (Igarashi et al. 2013; Lipatova and Campolattaro 2016).

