**FIGURE 1 fsn371640-fig-0001:**
[figure not shown]
Phase 1 study design.

After the pre‐test, participants will drink water to neutralize their mouths. Group A will receive 175 mg (half a tablet), Group B will receive 350 mg (one tablet), and Group C will receive 700 mg (two tablets) doses in MB tablets. Subjects will be instructed to dissolve the tablet with saliva on their tongue for 5 min and make contact with the tablet against as much surface area of the oral cavity as possible without chewing or swallowing it (Hudson et al. 2018). Immediately after dissolving, participants will receive the same solutions and food items used for the pre‐test to capture changes in perceived taste perception on gLMS.

#### Phase 2

3.7.3

A hypo‐palatable vegetarian salad containing half‐serve vegetables (raw broccoli and rocket leaves) and half‐serve fruits (Granny Smith apple), which are the minimum possible servings per Australian dietary guidelines (Brownie et al. 2015), will be prepared 30 min before the data collection time at Griffith University, Gold Coast campus kitchen lab or the Participants' home, based on the participants' preferences. Food items for the vegetarian salad and the Coca‐Cola (representing hyper‐palatable SSB) will be purchased from the local market. The food will be stored in a refrigerator (4°C), removed, and placed on separate plastic trays 10 min before each test. The SSB will be kept at room temperature, and 30 mL will be poured into 50 mL paper cups, which are clean and uniform in color (Mielby et al. 2018).

Figure 2 shows that participants (*n* = 40) will be allocated to four treatment arms (*n* = 10 in each group). The data collection procedure will follow these steps:

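### Phase 1 gives MB to every arm and is sized on a before-after test, so its pre-post change cannot by itself be read as an effect of MB

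*Protocol article*

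**What the plan says.** Table 1 of the protocol article describes Phase 1 as a "Three‐arm pre‐post parallel design" and lists its independent variable as "Different MB doses (175, 350, and 700 mg" only. Phases 2 and 3 are each a "Four‐arm placebo‐controlled single‐blind pre‐post parallel design", and Phase 4 is also placebo-controlled and single-blind. Phase 1 carries neither label.

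Section 3.7.2 gives MB to all three groups: "Group A will receive 175 mg (half a tablet), Group B will receive 350 mg (one tablet", and Group C two tablets. On the second tasting it says: "Immediately after dissolving, participants will receive the same solutions and food items used for the pre‐test to capture changes in perceived taste perception".

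Section 3.4.1 sizes Phase 1 with paired t-tests, using Cohen's d = 0.78 "on the sweetness taste perception obtained before and after taking MB", with 80% power, alpha 0.05 and 20% dropout, giving 54 participants (18 per group).

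Table 6 (Phase 1) plans a mixed model with dose as fixed effect, time as within-subject factor and participant as random effect, followed by Dunn-Šidák comparisons between doses. It names neither a dose-by-time term nor a contrast by acidity.

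Table 4 pairs near-neutral bitter and sweet stimuli with acidified versions. Its note explains the acidified mixtures "as an acidic pH was essential for the taste modification action of miraculin".

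**The concern.** The Phase 1 aim is to assess what different doses of MB do to taste perception. Two questions sit inside that aim: whether the doses differ, and whether MB changes taste at all.

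The parallel arms can answer the first. They cannot answer the second, because three equally effective doses would show no difference between them. Evidence of MB against nothing can come only from the time effect.

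The null behind that effect is that ratings stay the same on a second tasting of the same stimuli in the same session. Drift in how the scale is used, sensory adaptation or expectation could break that null when MB does nothing. Phases 2 and 3 have a placebo arm to absorb such shifts, but their test items are a salad and a soft drink, so they do not repair inferences about the Phase 1 solutions and single foods. The limitations in section 4 cover self-reported diet and do not mention this.

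**Working it through.** **1. Reproduce the stated size.** Inputs from section 3.4.1: d = 0.78, power 80%, alpha 0.05 (taken as two-sided), dropout 20%. For a paired t-test with n completers, the noncentrality is d × √n on n − 1 degrees of freedom.
- n = 14: power 77.0%.
- n = 15: power 80.2%. So 15 completers per group are needed.
- 15 × 1.2 = 18 per group, and 3 × 18 = 54.

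The stated figure reproduces on this route, so the hypothesis that Phase 1 is powered for is a mean change of zero. (Dividing by 1 − 0.2 would give 19 per group, 57 in total; that is a side matter.)

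**2. Rejection of that null with no MB effect.** Let s be a shift common to all participants, in SDs of the change score. The documents give no value, so s is an assumed range. The noncentrality is s × √n, two-sided at 5%.

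| Assumed shift s | One arm, n = 15: s√n | Rejects | Pooled, n = 45: s√n | Rejects |
|---|---|---|---|---|
| 0 | 0 | 5% | 0 | 5% |
| 0.2 | 0.77 | 11% | 1.34 | 26% |
| 0.3 | 1.16 | 19% | 2.01 | 50% |
| 0.5 | 1.94 | 44% | 3.35 | 91% |

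The table uses planned completers (15 per arm, 45 in total). If all 18 per arm completed, the per-arm rates would be 13%, 23% and 52%, and the pooled rates over 54 would be 30%, 58% and 95%.

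**3. The same shift in a between-arm comparison of change.** A simulation with 15 per arm and 40,000 runs gave 4.9% to 5.0% rejection at common shifts of 0, 0.2 and 0.5 SD. Drift that is equal in all arms cancels if the comparison is made on change.

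**4. What the plan could use as an internal control.** From Table 4:

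| Stimulus | Near-neutral pH | Acidified pH |
|---|---|---|
| PROP solution | 6.80 | 2.70 |
| Broccoli | 6.92 | 4.00 |
| Sucrose solution | 7.00 | 3.02 |
| Maple syrup | 6.78 | 3.27 |

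If miraculin needs acid, the change on the near-neutral member estimates repeat-tasting drift within the same person. Sour and tart stimuli have no such pair.

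**5. Price of that contrast.** Assume that the two changes have equal SDs and correlation r. The standard error of their difference is √(2(1 − r)) times that of one change.
- r = 0: factor 1.41, effective d = 0.78 / 1.41 = 0.55, power with 15 completers 51%.
- r = 0.25: factor 1.22, effective d = 0.64, power 63%.
- r = 0.5: factor 1.00, power 80%.

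These powers also assume that the full 0.78 effect falls on the acidified member and none on the neutral one.

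**The case against.** **The design is declared.** The article calls its phases quasi-experimental, labels Phase 1 openly as pre-post, and puts placebo control in the later phases. That stands, and the point is not that Phase 1 must be redesigned. It concerns what the time effect may be said to show.

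**The paired t-test is not the planned analysis.** A reader might infer that each dose will be declared effective from its own paired test at 5%. Table 6 lists no such test. It plans a mixed model and comparisons between doses, so the per-arm rates illustrate the hypothesis used for sizing. The pooled rates are closer to a time effect in the model. Nor is every Phase 1 conclusion contaminated: dose comparisons made on change are protected against common drift, though not against expectation that grows with the number of tablets.

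**Phase 1 is not stated to be open-label.** A reader might infer that participants know they have taken MB. Table 1 is silent on blinding for Phase 1 and the arms differ visibly in tablet number, but participant information is not shown. The supportable statement is that blinding is not stated.

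**Some mitigation exists.** Participants rinse between stimuli, drink water before the tablet, spend 5 minutes dissolving it, and set the scale's boundaries before rating. These steps bear on adaptation and scale use. They do not address expectation, and they do not supply a comparator.

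**The acidity comparison may already be intended.** Section 4 promises evidence on the low-pH requirement, so it cannot be said that the pairs were overlooked. Table 6, however, ties no contrast to that promise.

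**The acidified pairs are an imperfect control.** This stands. Each mixed solution holds 5 mL of PROP or sucrose solution where the neutral one holds 10 mL, so half the tastant, with sourness added. In the food pairs the broccoli and syrup amounts are unchanged, but lime juice is added. An expectation that sour turns sweet would act mainly on the acidified member and would not cancel. The Introduction also calls earlier findings on bitter and sweet tastes inconsistent, so a zero MB effect on the neutral member is an assumption.

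**Conclusion.** The point holds in a limited form. Phase 1 has no arm without MB, its size rests on a before-after null, and the article neither names the term that would give controlled dose comparisons nor acknowledges that the pre-post change is uncontrolled.

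The rejection rates in the working depend wholly on the assumed shift. At the low end, 0.2 SD, the per-arm rate is about double the nominal 5%; pooled over the arms, or at larger shifts, it is well above that. They show sensitivity and do not predict the trial's error rate.

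The documents do not support the stronger readings that Phase 1 is unblinded, that its dose comparisons are invalid, or that the acidity contrast could replace the pre-post result. That contrast can support interpretation for bitter and sweet stimuli only.

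**What to change.** In Table 6, Phase 1:

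1. Make the between-dose comparisons on change from pre-test, by naming the dose-by-time term as the one to which the Dunn-Šidák comparisons apply.
2. Report the pre-post change as uncontrolled, and do not present it on its own as an MB effect. For sour and tart stimuli, limit claims of effect to dose differences in change.
3. For the bitter and sweet stimuli, add a supporting within-participant negative-control analysis: change on the acidified stimulus minus change on its near-neutral counterpart (time-by-acidity, by dose).
4. State that analysis's limits: the acidified solutions hold half the PROP or sucrose; expectation specific to sour items is not removed; no MB effect on the neutral member is assumed; and the standard error is about 41% larger if the two changes are uncorrelated.

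Also state in Table 1 or section 3.7.2 whether Phase 1 participants are blinded to dose or product.

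The cost is a revision of wording and one added analysis, with no new participants or measurements. The changes remain possible if data collection has finished, in which case the added contrast should be marked as specified afterwards. The price is more modest conclusions, above all for sour and tart stimuli.
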